## Abstract

**Background:**

Depression is a leading cause of disability worldwide. To reduce the societal burden and improve quality of life for individual patients, treatments for depression need to be optimized. There is a particular need for person-tailored interventions that reinforce self-management of patients. Systematic self-monitoring and personalized feedback through the Experience Sampling Method (ESM) could provide such a person-tailored, empowering intervention that enhances treatment outcomes. The primary aim of this study is to investigate the efficacy of self-monitoring and personalized feedback as an add-on tool in the treatment of depressive complaints in a natural setting.

**Methods:**

The ZELF-i study is a pragmatic multi-site randomized controlled trial (RCT). We aim to recruit 150 individuals with depressive symptoms aged between 18 and 65 years, who have an intake for outpatient basic or specialized treatment at a mental health care organization in the North of the Netherlands. After the intake, participants will be randomly allocated to one of three study arms: two experimental groups engaging in 28 days of systematic self-monitoring (5 times per day) and receiving weekly personalized feedback on positive affect and activities (“Do”-module) or on negative affect and thinking patterns (“Think”-module), and a control group receiving no additional intervention. Self-report inventories of depressive symptoms, psychosocial functioning and feelings of empowerment will be administered before and after the intervention period, and at follow-up measurements at 1, 2, 3 and 6 months. The patient-experienced utility of the intervention will be investigated by a combination of quantitative and qualitative research methods.

**Discussion:**

The present study is the first to examine the effects of add-on self-monitoring and personalized feedback on depressive complaints in clinical practice. It is also the first to evaluate two different ESM modules targeted at both of depression’s core symptoms. Lastly, it is the first study that uses a combination of qualitative and quantitative methods to evaluate the patient-experienced utility of ESM with personalized feedback as an intervention for depression. Results of the present study may improve treatment for depression, if the intervention is found to be effective.

**Trial registration:**

Dutch Trial Register, NTR5707, registered prospectively 1 February 2016.

**Electronic supplementary material:**

The online version of this article (10.1186/s12888-018-1847-z) contains supplementary material, which is available to authorized users.

## Background

According to the World Health Organization, the leading cause of disability worldwide is depression [1], a common mental disorder that is characterized by two core symptoms: depressed mood and decreased interest or pleasure in activities [2]. Optimizing treatments for depression will reduce the societal burden and improve quality of life for individual patients. There is a particular need for cost-effective, personalized interventions that support the mental health care sector and reinforce self-management of patients (e.g., [3, 4]). Systematic self-monitoring and personalized feedback on contextualized patterns of affect through the Experience Sampling Method (ESM) could provide such an empowering, low-cost intervention.

With ESM, a patient gathers a multitude of prospective in-the-moment daily life assessments on affect, behavior, and context [5, 6]. Through aggregation of these systematically collected data, ESM can generate information that goes beyond what has been explicitly listed by the patient. Moreover, sophisticated analyses such as time-series analyses can determine the temporality of effects within a specific person, for instance, whether increased positive affect (PA) precedes or follows an increase in physical activity. ESM has generated important scientific insights in daily life emotional dynamics in depressed patients (for reviews see [7, 8]). Even more importantly, ESM also has great potential for clinical practice and the individual patient, because it allows personalized feedback (e.g., [9–11]. Small-scale proof-of-principle studies have underlined the potential of this approach for the individual patient (e.g., [10, 12, 13]). Kauer and colleagues [14] investigated the efficacy of self-monitoring and feedback on mood, stress, and daily activities as a therapeutic tool for adolescents with emotional or mental health issues in a larger study (*n* = 114). They found that, compared to the control group (which only monitored daily activities), emotional self-awareness increased more in the intervention group, which in turn decreased depressive symptoms. More recently, a pioneer randomized controlled trial (RCT) established the efficacy of ESM as a therapeutic tool for patients with depression (*n* = 102, [15]). That is, add-on ESM-derived personalized feedback on PA and activities resulted in a significantly and clinically relevant stronger decrease in depressive symptoms compared to pharmacological treatment alone. While promising, the ESM intervention was evaluated in the absence of psychotherapy, which is a common part of depression treatment, and had an extensive face-to-face component itself. Therefore, it is not yet known whether ESM as a self-management tool could have added positive effects to treatments in regular clinical practice. In addition, data acquisition as well as data analysis for the personalized feedback reports were a laborious exercise, hampering use in clinical practice.

We will take the necessary steps to move ESM-derived personalized feedback closer towards implementation as a therapeutic tool for depression in this study, which is named the ZELF-i project to emphasize the self-management aspect of our approach (self = *zelf* in Dutch, *i* stands for intervention). First, we will optimize the ESM intervention for clinical practice by making it easily accessible on patients’ own smartphones and by reducing personnel investment through automatized personalized analyses and digital feedback reports. Second, we will reexamine the previously reported efficacy of ESM-derived personalized feedback on PA and activities (ESM “Do-module”) in an RCT embedded in a naturalistic clinical context. Third, we will examine the efficacy of an alternative ESM module focused on negative affect (NA) and thinking patterns (ESM “Think-module”). Until now, there have only been studies with one specific module or a general set of items. Therefore, it is unknown whether the form (systematic self-monitoring) or the content of an ESM module is relevant. Our two ESM modules are both conceivably beneficial, as they link up with the two main angles of psychotherapy for depression: behavioral activation through positive reinforcement of activities, and cognitive therapy aimed at helping individuals recognize and replace negative thinking patterns [16].

Self-monitoring and personalized feedback through ESM is a potential improvement for depressed patients for several reasons. First, previous studies suggest clear health benefits in terms of a decrease in depressive symptoms [14, 15]. Second, in contrast to pharmacotherapy, the intervention mobilizes patients as active agents in their process to recovery, as evidenced by increases in feelings of empowerment [17]. Third, the intervention supports patients outside the clinician’s office, in their daily lives, which is where changes should occur. Fourth, person-tailored approaches should become the new focus in mental health care according to national and international directives (e.g., [4]) and patient organizations (e.g., *Landelijk Platform GGZ*). The intervention meets this need by providing personalized feedback on relevant aspects of daily life such as diurnal mood fluctuations, affective reactivity to social and physical activities, and the activation of negative thinking patterns in response to sad mood. Fifth, patients can start directly after intake, making the most out of the commonly long wait list period at mental health organizations [18]. Considering that patients usually start seeking professional care out of a sense of urgency, we hope that it will be satisfactory to them that they will be able to start working on their problems directly, without a period of passive waiting. Sixth, by bringing their feedback reports in at the start of the treatment, patients could commence specialized mental health care programs with a kick-start. By already having monitored their thoughts and feelings in relation to their activities for a couple of weeks, they are likely to have acquired a better insight in the processes involved in their depressive symptoms and day-to-day functioning than patients who did not partake in self-monitoring. Seventh, no costly equipment is required, only a working smartphone, which means the intervention could potentially reach many patients seeking care. In fact, interest among psychiatric outpatients in using smartphones to monitor their mental health is high [19].

According to guidelines for the development of evidence-based directives, two independently performed high-quality RCTs of substantive size provide the highest level of proof for the efficacy of an intervention [20]. Thus, the proposed RCT could provide more definitive answers regarding the efficacy of ESM as a therapeutic tool for depression. While a reduction in depressive symptomatology is important, we believe ‘health’ goes beyond the traditional definition as the absence of illness. ESM-derived personalized feedback could assist patients in actively trying to gain more control over their own psychological problems and enhance their functioning as evidenced by increases in feelings of empowerment [17] and increased engagement in social activities [21]. These functional outcomes are at least as relevant as clinical outcomes, as for many patients the essence of recovery is to rise above the presumed limitations associated with mental illness [22]. In fact, more and more voices are calling for a reformulation of ‘health’ into the ability to adapt and to self-manage in the face of social, physical and emotional challenges (e.g., [23]). Therefore, we will examine the impact of the ESM intervention not only on depressive symptoms, but also on measures of functioning and empowerment.

When evaluating an intervention not only the efficacy on a group level is important, but the perspective of individual patients also needs to be taken into account [24]. Qualitative methods in which the experiences and opinions of patients are at the center, should be an essential component of health care research [25]. Qualitative research based on interviews with patients has shown that an active attitude towards rehabilitation and structured attention to oneself are important themes for individuals with depression [26, 27]. ESM with personalized feedback could meet these wishes, but there has been virtually no research on patient experiences with such an intervention, except for a personal case study by Peter Groot [10]. He describes how self-monitoring of his mood helped him in his recovery process as follows (p. 354): *“I now look at my own mood swings in a different way. I can accept more easily the gloomy periods I still have once in a while; they are briefer, I get through them more easily, and I think they occur less frequently than in the past. I feel better ‘protected’ and more ‘empowered’ against the vulnerability with which I have apparently been cursed.”* It is not known whether these experiences generalize to other individuals. Therefore, a secondary aim of the ZELF-i project is to evaluate the patient-experienced utility of ESM with personalized feedback through patient interviews.

## Methods

ZELF-i is a multi-site trial designed according to the principles of a pragmatic RCT to allow evaluation of the intervention in real-life care facilities. Details are described below according to the SPIRIT guidelines [28]. The study was approved by the Medical Ethical Committee of the University Medical Center Groningen (no. 2015/530). The trial has been registered prospectively in the Dutch Trial Register (Nederlands Trial Register, NTR5707, http://www.trialregister.nl) at 1 February 2016.

### Participants

We will recruit 150 male and female adult patients referred for depressive complaints to general or specialized outpatient teams at mental health care organizations in the North of the Netherlands. Participants will be recruited within the research network of mental health institutions in the North of The Netherlands, the Rob Giel Research Center (https://www.rgoc.nl), which covers a catchment area of over 4 million inhabitants. Eligibility criteria are broad to include typical patients. Inclusion criteria are: a) indication for depression treatment by the mental health care professional (hereafter named: practitioner); b) age between 18 and 65 years; and c) written informed consent. Exclusion criteria are (based on practitioners’ appraisals): a) crisis intervention warranted (i.e., in the case of acute suicidality); b) presence of psychotic or manic symptoms; and c) incapability of following research procedures due to inadequate Dutch language proficiency, significant auditory or visual impairments or mental retardation. Patients will be enrolled in regular treatment upon availability, that is, the start of regular treatment will not be postponed until participation in ZELF-i finishes. The ZELF-i intervention is intended as an add-on tool at the start of care as usual and thus circumstances are otherwise kept as ‘natural’ as possible. Participants will receive travel reimbursements and an additional €10 if they used the data bundle of their own smartphone to participate in the intervention.

### Procedure

#### Recruitment

An overview of the study design is presented in Fig. 1. Individuals scheduled for intake at one of the participating mental health care teams will receive an information letter about ZELF-i and a contact consent form together with their intake invitation. Through the information letter, participants will be made aware of the procedure that, at the end of the intake, the practitioner will discuss the possibility to participate in ZELF-i with them if a) depression treatment is indicated, and b) the practitioner deems ZELF-i suited for the patient. Participants will be made aware that participation is voluntary and refusal to participate will not affect their treatment. Patients decide independently whether they are interested in the research and want to be contacted by the research team by sending back the consent form or bringing it to the intake at the mental health care institution. It is important that eligible participants are enrolled in the study shortly after the intake, because the intervention (28 days) is designed to support participants early on and bridge potential waiting periods between the intake and the start of the indicated depression treatment in a constructive way. Therefore, eligible participants will be contacted by a research assistant preferably within a few days after the intake to answer any questions and schedule an appointment for the introduction session of the intervention study.

**Fig. 1 Fig1:**
[figure not shown]
Overview of the design of the randomized controlled trial. ESM = Experience Sampling Method. * The interview is optional and will take place before the 2 month follow-up. ** The time interval between the start date of the participation in ZELF-i and the start date of regular treatment varies between participants

#### Introduction session and baseline measurement

The introduction session will take place at the mental health care organization. At the start of the introduction session, participants will have another opportunity to ask questions about the study procedures. If everything is clear, they will be asked to provide written informed consent. After the informed consent procedure, participants will be randomly allocated to the control group or one of two ESM intervention groups. Then, detailed instructions and practice runs for the ESM modules follow, depending on the allocated treatment condition. Finally, all participants will fill out questionnaires assessing characteristics at baseline, depressive symptomatology, functioning, empowerment, and questionnaires necessary for cost-effectiveness analyses (see Study Parameters section).

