#### Randomization

Participants will be randomly allocated to the control group or one of two ESM intervention groups (“Do-module” and “Think-module”). Randomization (allocation ratio 1:1:1) will be stratified per treatment location according to the duration of antidepressant pharmacotherapy (new/switch vs. maintenance, i.e., receiving antidepressant or mood stabilizing medication for less vs. longer than 8 weeks prior to study entry), and current psychotherapy (yes or no). For these different strata, separate blocks with an allocation sequence of six with an equal condition distribution will be created using an online randomization tool (https://www.random.org/lists). Thus, each of the three conditions will be present twice in a block of six. The allocation will be implemented by using sequentially numbered sealed envelopes (i.e., one pile of envelopes for each stratum). The allocation will be done during the introduction session, by team members who do not have access to the allocation sequence. Participants and research assistants are obviously not blind to treatment. Practitioners are not blind to treatment per se; participants decide themselves whether they want to discuss their feedback reports with their (future) therapist.

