#### Main study parameter

The primary outcome measure to determine efficacy of the intervention will be the change in depression symptom severity as measured by the self-report Inventory of Depressive Symptomatology (IDS-SR, [31]) across 6 time points: baseline, after 4 weeks of ESM and at 4 follow-up measurements at 1, 2, 3, and 6 months (post-ESM). Participants will be followed prospectively to compare the efficacy of the intervention modules mutually and to the control group.

The 30-item self-report **Inventory of Depressive Symptomatology (IDS-SR)** includes all DSM-IV [2] diagnostic criterion items for major depressive disorder, as well as commonly associated symptoms such as irritability [31]. Each symptom item is scored on a scale from 0 to 3, with higher scores denoting greater symptom severity. The time frame for assessing symptom severity is the 7 day period prior to assessment (independent of whether symptoms have been long-standing, chronic, or recent). The IDS-SR is scored by summing the item responses. Either appetite increase or decrease, and either weight increase or decrease are used to calculate the score. If increase and decrease items are both completed, the highest of the two scores is used. The IDS-SR has good psychometric properties with high concurrent and internal validity (Cronbach’s α = .92) and is sensitive to treatment change [31, 32].

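### The baseline IDS-SR is completed after participants learn their arm and, in the ESM arms, after module practice, so it is open to response bias of unknown size and direction

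*Protocol article*

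**What the plan says.** The section on the introduction session and baseline measurement in the protocol article fixes the order of events within one visit:

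1. Consent, then allocation: "After the informed consent procedure, participants will be randomly allocated to the control group or one of two ESM intervention groups".
2. Training by arm: "Then, detailed instructions and practice runs for the ESM modules follow, depending on the allocated treatment condition".
3. Questionnaires last: "Finally, all participants will fill out questionnaires assessing characteristics at baseline, depressive symptomatology, functioning, empowerment", together with the instruments for the economic evaluation.

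The Randomization section confirms the timing ("The allocation will be done during the introduction session, by team members who do not have access to the allocation sequence") and the lack of blinding ("Participants and research assistants are obviously not blind to treatment"). Under Main study parameter, "The primary outcome measure to determine efficacy of the intervention will be the change in depression symptom severity" on the self-rated IDS-SR. It is measured at six time points, of which this baseline is the first. The section on efficacy of the ESM-modules analyses the six scores by a multilevel model with a time-by-group interaction, and analyses the OQ-45 and NEL in a similar way. Nowhere does the text place an IDS-SR before allocation.

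**The concern.** A baseline should be untouched by the treatment assignment. Here each participant rates their own symptoms just after learning whether they will get an ESM module or nothing extra. Two of the three arms have also just been trained on items that begin with current mood. In the Think-module these go on to hassles and uplifts and to positive and negative thoughts.

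Three mechanisms are plausible, and they do not point the same way (a higher IDS-SR is worse):

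- Controls disappointed by their allocation may score higher at baseline. Their later improvement then looks larger, which works against the intervention.
- ESM participants encouraged by their allocation may score lower at baseline. Their later improvement then looks smaller, which also works against the intervention.
- Practising mood items may raise baseline scores in the ESM arms, which would favour the intervention. The article itself notes, when it introduces the LEIDS-R, that attention to mood may set off negative thinking in cognitively reactive people.

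The baseline is one of the six points that determine the time-by-group interaction, so an arm-related shift there carries into the primary contrast, and likewise for the OQ-45 and NEL.

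**Working it through.** **The plan's own figure.** The point rests on the order of procedures and not on any stated number. The section on group analyses claims 85–99% power for 3–10 points with 40 per group, alpha 0.05 and a pre-post correlation of 0.6. It gives no SD, so the claim can only be solved backwards. For a change score the standard error of the arm difference is SD × √(2(1 − 0.6)) × √(2/40) = SD × 0.894 × 0.224 = 0.2 × SD. Two-sided (the article does not state sidedness), 85% at 3 points needs an SD of about 5.0, and 99% at 10 points needs about 11.7. I use SDs of 5 and 10 below as assumptions.

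**Bias from a shift.** Let b be the mean baseline difference between an ESM arm and control that is caused by knowing the arm or by the practice. The documents give no value. I take 0.5 to 2 points as an assumed range.

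- Change-score contrast: size b.
- Baseline-adjusted contrast (ANCOVA): correlation × b = 0.6b, assuming equal SDs before and after.
- Linear slope over the six measurements: the times are 0, 4, 8.3, 12.7, 17.0 and 30.1 weeks, taking 4 weeks of ESM and follow-up at 1, 2, 3 and 6 months of 4.345 weeks each. Their mean is 12.02 and the sum of squared deviations is about 573.8. The least-squares weight of the baseline is −12.02/573.8 = −0.021 per week. The slope difference is thus biased by 0.021b per week, or 0.021 × 30.1 × b = 0.63b over the whole period.

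| Assumed b | Change score | ANCOVA | Linear slope over 30 weeks | False-positive rate, change score, SD 5 | Same, SD 10 |
|---|---|---|---|---|---|
| 0 | 0 | 0 | 0 | 5.0% | 5.0% |
| 0.5 | 0.5 | 0.3 | 0.32 | 7.9% | 5.7% |
| 1 | 1.0 | 0.6 | 0.63 | 17.0% | 7.9% |
| 2 | 2.0 | 1.2 | 1.26 | 51.6% | 17.0% |

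The false-positive rates are two-sided with 40 per arm and standard errors of 0.2 × 5 = 1.0 and 0.2 × 10 = 2.0. For b = 1 and SD 5: 1 − Φ(1.96 − 1) + Φ(−1.96 − 1) = 17.0%. They apply to a change-score test. The multilevel model would need variance components that the article does not give.

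**Effect on power.** At SD 5 with a true 3-point benefit, a 1-point shift against the intervention lowers power from 85% to Φ((3 − 1)/1.0 − 1.96) = 52%. A 1-point shift in its favour raises it to 98%.

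**Which row fits the plan.** The planned model is the time-by-group slope, so the slope column is the closest guide. The model may also use a quadratic term in time, for which I have not computed a figure.

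**The case against.** The strongest reply is that the trial is openly unblinded and self-reported throughout. Knowledge of the arm can colour the five later measurements too, and the article already concedes a possible effect of extra attention. It adds that the IDS-SR refers back in time ("The time frame for assessing symptom severity is the 7 day period prior to assessment"), so news received minutes earlier may move it little. Much of this stands: the shift may be small, and its sign is unknown. But later knowledge of the arm cannot be avoided in this design, whereas knowledge at baseline can.

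A reader might infer more than the text supports:

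- **That the damage cannot be undone by analysis.** It can: post-baseline scores can be compared between randomised arms without using this baseline.
- **That the whole shift passes into the result.** This is true of a simple change score. For the planned linear slope it is about 0.63 of the shift over 30 weeks.
- **That the shift would create a false benefit.** Two of the three mechanisms would hide a benefit.
- **That allocation itself is compromised.** Sequentially numbered sealed envelopes are used, by staff without access to the sequence. The issue is response bias, not selection.
- **That the TAS-20 and LEIDS-R are spoiled as pre-treatment measures.** The article names no analysis that uses them and describes alexithymia as a personality construct. Nothing shows that these scores would move within one session.

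Fig. 1 and the supplementary table of measurement times are not available here, but the text on the order is explicit.

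**Conclusion.** The point holds as an avoidable exposure to response bias, not as a demonstrated bias. The stated order makes the baseline IDS-SR, OQ-45 and NEL post-randomisation self-reports by unblinded participants, and the primary model uses the IDS-SR baseline as its first time point. For an assumed 1-point shift the bias is roughly 0.6 to 1 point depending on the analysis, that is 20% to 33% of the 3-point lower target (0.6/3 and 1/3). The size of the shift is an assumption and its direction is open. The SDs behind the error rates are also assumed. The case for acting is that the correction is nearly free, even if the true shift proves small.

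**What to change.** Reorder the introduction session: consent, all baseline questionnaires, opening of the envelope, then module instructions and practice. The visit, the instruments and the sample size of 150 are unchanged. Some information has to be collected before allocation in any case, because medication duration and current psychotherapy decide which pile of envelopes is used.

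If participants have already been enrolled in the stated order:

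- Keep them in the analysis. Excluding them could discard much of the sample.
- Report the order in which baseline was taken.
- Compare baseline scores by arm, as description only. With 50 per arm the standard error of a difference is SD × √(2/50) = 0.2 × SD, or 1 point at SD 5 and 2 points at SD 10. A 1-point shift could not be told from chance.
- Add a sensitivity analysis of post-baseline scores that does not use this baseline. Compare levels between arms, not slopes, because a slope over post-baseline scores alone would miss a benefit already present at the end of the ESM period.

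The cost of that analysis is precision. For a single follow-up at correlation 0.6 the standard error is 1/0.894 = 1.12 times that of a change score and 1/0.8 = 1.25 times that of ANCOVA. At SD 5, power for 3 points falls from 85% (change score) to about 77%.
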